## Abstract

**Highlights:**

**What are the main findings?**
This approach supports motor recovery while also facilitates the transfer of learned skills to meaningful daily life activities.A focus on functional performance allows rehabilitation to be directly aligned with MS patients’ daily life needs and priorities.

**What are the implications of the main findings?**
Clinicians should address not only physical impairments but also how MS affects daily activities and functionality.

**Abstract:**

**Objective**: The aim of this study will be to evaluate the effectiveness of a task-oriented training program in improving functional performance and health outcomes in patients with MS. **Methods**: A pilot randomized clinical trial will be conducted according to SPIRIT guidelines. Participants will be randomly assigned to the experimental group or the control group. Assessment and treatment will take place at patient association facilities or research center. Participants diagnosed with MS by a neurologist and meeting the inclusion criteria will be invited to participate voluntarily. The experimental group will undergo an 8-week TOT intervention, twice weekly, 45 min. The control group will maintain usual care and be given a fatigue management pamphlet. The main variable in this study will be the Canadian Occupational Performance Measure. The level of fatigue will be assessed with the Modified Impact Fatigue Scale and the Fatigue Severity Scale, upper limb strength using the Arm Curl Test, hand and pinch dynamometer, motor speed with the Finger Tapping Test, manual dexterity with the Nine Hole Peg Test, Purdue Pegboard Test and the Coin Rotation Test. Satisfaction and adherence with the intervention will be recorded with the Sport Injury Rehabilitation Adherence Scale. **Results**: The results will be published as a peer-reviewed article. **Conclusions**: The present protocol aims to fill a relevant gap in the literature, offering a structured intervention based on task-oriented training principles, specifically tailored to the functional and occupational needs of people with MS.

## 1. Introduction

Multiple sclerosis (MS) is a chronic, progressive, and demyelinating disease of the central nervous system. It is considered one of the most common non-traumatic disabling diseases that affects young adults [1]. This disease causes sensorimotor, visual, cognitive and autonomous dysfunctions [2]. Of particular relevance, fatigue stands out as one of the most prevalent and disabling symptoms among MS patients and causes interference with patients’ daily functioning [3]. Upper extremity function, manual dexterity, and walking ability are also recognized as key predictors of perceived difficulties in performing daily activities among individuals with MS [4]. It significantly affects health and leads to a wide range of impairments in body functions, limitations in activities, and restrictions in participation [5]. As a result, the performance of daily life activities may be considerably compromised, thereby increasing the need for care and support for these patients.

In this context, task-oriented training (TOT) interventions have emerged from the movement science and motor skill learning literature [6]. This perspective of rehabilitation focuses on improving performance in functional tasks through mass goal-directed practice and repetition of activities that are of high intensity and meaningful to the patient. Bayona et al. [7] reported the importance of TOT interventions, noting that the most effective way to relearn a task is to train specifically for that task. It has been developed within the literature of motor control and learning, with increased evidence of neural plastic changes as a result of this training being shown [8]. Previous studies have underscored that TOT seeks to enhance cortical reorganization, remediation and the reacquisition of functional skills by encouraging active problem-solving, while systematically varying environmental conditions, feedback and task difficulty to improve performance [9].

The efficacy of TOT interventions has been previously demonstrated in some studies showing improvements in different health outcomes, such as upper limb function [10], manual dexterity [11], and walking endurance [12], among MS patients. However, authors have highlighted the need for additional research to strengthen the current body of evidence. While TOT has been widely implemented and extensively studied in stroke patients, its application in MS remains in the early stages. Therefore, this study aims to evaluate the effectiveness of a TOT program in improving functional performance and health outcomes in patients with MS.

## 2. Materials and Methods

### 2.1. Study Design

A pilot randomized clinical trial will be conducted in accordance with the guidelines of Standard Protocol Items: Recommendations for Interventional Trials (SPIRIT) [13]. The study is registered at clinicaltrials.gov with the code NCT07106255.

### 2.2. Ethical Aspects

This study will comply with and respect the principles established in the Declaration of Helsinki of 1964 and its subsequent amendment in 2013 (World Medical Association, 2013) [14], which states that the purpose of biomedical research involving human subjects must focus on “improving diagnostic, therapeutic, and prophylactic methods, as well as the understanding of the etiology and pathogenesis of diseases.” Similarly, the study will adhere to the International Ethical Guidelines for Biomedical Research Involving Human Subjects of 1982. These guidelines emphasize the protection of the most vulnerable communities to ensure that the rights of every age group or individuals with specific pathologies are respected. The study will also comply with the provisions of Organic Law 3/2018 of 5 December on the Protection of Personal Data (LOPD), ensuring the confidentiality of the data of the participants included in the study. A certificate from the Regional Ethics Committee (Andalusian Biomedical Research Ethics Portal) was obtained with code 2036-N-23.

### 2.3. Participants

Participants with MS will be invited to voluntarily participate in different patient associations. They will be informed about the objective and development of the study and sign an informed consent prior to their inclusion. The inclusion criteria for the MS group will include the following: (1) Diagnosis of Multiple Sclerosis by a neurologist according to the 2024 revisions of the McDonald Criteria [15]. These criteria require evidence of dissemination in space, defined by typical lesions in at least two of five anatomical locations within the central nervous system (CNS) (periventricular, cortical or juxtacortical, infratentorial, spinal cord, and optic nerve). Diagnosis must be confirmed by the presence of dissemination in time or evidence of intrathecal antibody production (demonstrated by cerebrospinal fluid-restricted oligoclonal bands or a positive kappa free-light chain index). Alternatively, MS may be diagnosed if patients show typical clinical presentations involving four or more typical CNS anatomical locations, or through the identification of specific MRI biomarkers such as the central vein sign or paramagnetic rim lesions in required clinical and radiological contexts. (2) Participants must be aged over 18 years old. (3) Participants must accept and sign the informed consent. Participants will be excluded if they present (1) a cognitive level or condition that did not allow for completion of the evaluations; (2) an exacerbation of MS during the previous 3 months; (3) the presence of interfering musculoskeletal, neurological, orthopedic, and/or rheumatic disorders affecting hand and/or finger mobility, including previous trauma or fracture of the upper extremity. Recruitment will remain open until July 2026.

### 2.4. Procedures and Measures

The evaluation and the intervention will be conducted either in the facilities provided by the MS associations participating in this study or in the facilities of the research center. The specific location will be selected according to the participant’s preference, to facilitate accessibility and adherence to the intervention. The participant timeline, including the schedule of enrollment, interventions, and assessments, can be found in Figure 1.

#### 2.4.1. Allocation

After eligibility assessment, participants will be randomly assigned to either the experimental group or the control group. Allocation will be determined by using a computer-generated random number list with the software www.random.org.

#### 2.4.2. Experimental Group

Participants included in the experimental group will undergo an 8-week TOT intervention, administered twice weekly, with each session lasting 45 min. TOT “*is an effective rehabilitation intervention that focuses on the use of client-centered, repetitive practice of activities that are of high intensity and meaningful to the client*” [9]. The TOT intervention will be designed based on a previous study [16] that established guidelines for its implementation in clinical practice. Within this framework, the intervention will comprise sessions involving meaningful and repetitive activities tailored to both the patient and their specific context. The tasks included in the intervention sessions will be chosen by each participant based on the occupations identified through the Canadian Occupational Performance Measure (COPM) [17] tool during the initial assessment. Through the COPM semi-structured interview, participants will identify daily activities they find difficult to perform and rate their importance on a 10-point scale. The three activities rated as most important by the participant will be selected as the primary treatment goals. This client-centered selection process directly dictates the content of the intervention, ensuring that all sessions will be tailored to practice and improve the specific daily activities chosen by the participant. The tasks derived from the three selected occupations will be randomly organized and focused on their complete reconstruction. To support the intervention, a range of custom-designed materials will be employed, alongside therapeutic tools and materials such as therapeutic putty, TheraBand, and other tools commonly used in physical rehabilitation interventions. Throughout the intervention, participants will receive positive reinforcement that will fade over time to prevent unnecessary dependency. To ensure optimal therapeutic dosing and standardize difficulty progression across participants, task intensity will be monitored using the Borg Rating of Perceived Exertion (RPE, 6–20) scale [18]. This tool consists of a scale from 0 to 20 levels of perception, with the number 6 being ‘very, very light’, while a value of 20 is considered as ‘very, very hard’. The complexity of the selected task will systematically be increased only when the participant consistently reports a perceived exertion level of 11 (“Fairly light”) while performing the task. Conversely, the complexity will decrease if the participant reports a level of 17 (“Very hard”). The use of this standardized threshold ensures that all participants remain in an optimal challenge zone for motor learning and neuroplasticity, dictating the moment for task progression regardless of the specific nature of the practiced occupation [19,20]. Once the participant achieves and maintains a perceived exertion level of 11 on the Borg scale, the therapist implements systematic modifications to progress the difficulty or introduce contextual interference. To standardize these modifications across the entire sample, regardless of the selected occupation, therapists will use the task-adjustment parameters described in Supplementary Materials.

#### 2.4.3. Control Group

Participants included in the control group will continue with their usual treatment and will receive a pamphlet containing information on fatigue management. The selection of usual care as a comparator will be based on the pragmatic nature of the research question, which seeks to evaluate the effectiveness of the intervention against existing clinical practices. By utilizing this design, we aim to measure the incremental benefit of the intervention relative to the outcomes of patients receiving individualized care in a real-world clinical environment [21].

#### 2.4.4. Descriptive Measures

An independent researcher, blinded to the patients’ group allocation, will collect all data at baseline and after the intervention. To characterize the clinical profile of the participants included in the study, the Expanded Disability Status Scale (EDSS) [22] and the ‘symptoMScreen’ [23] will be used. The EDSS is a widely used method for quantifying disability in individuals with multiple sclerosis. It ranges from 0 (normal neurological function) to 10 (death due to MS), based on neurological examination and the assessment of ambulation and functional systems. The ‘symptoMScreen’ tool consists of 12 domains, each rated on a 7-point Likert scale ranging from 0 (not affected at all) to 6 (total limitation/unable to perform most daily activities). In addition, sociodemographic and anthropometric characteristics will also be collected, including age, sex, and type of MS.

#### 2.4.5. Outcome Measures

The primary outcome in this study will be the Canadian Occupational Performance Measure (COPM) [17]. This tool measures the perception of problems related to the overall quality of performance, development and satisfaction with particular occupations. This is a standardized instrument that was previously validated [17,24] and used [25] in MS patients. The COPM will be used under a formal license that will be obtained through official channels to ensure full compliance with copyright and intellectual property regulations.

The secondary outcomes include fatigue level, upper limb strength, motor speed and manual dexterity. The level of fatigue will be assessed with the Modified Impact Fatigue Scale (MFIS) [26] and the Fatigue Severity Scale (FSS) [27]. The MFIS consists of items from which a total score is obtained and for each subscale. Scores range from 0 to 36, with higher scores indicating a greater impact of fatigue on activities. The FSS consists of nine items that are rated on a scale of 1 to 7. A higher score indicates a higher agreement with the statement presented in each item. This scale is recommended for use in clinical practice and research in MS patients [26,28].

Upper limb strength will be assessed using the Arm Curl Test (ACT) [29], a hand dynamometer, and a pinch dynamometer. These tests have previously been used in MS research [30,31]. The ACT consists of performing as many arm curls as possible in 30 s while sitting in a chair. The dynamometer and hand dynamometer measure grip and pinch strength respectively. Motor speed will be assessed with the Finger Tapping Test (FTT) [32]. In this test, the number of fingers taps the participant can perform in three attempts of 20 s each is counted. Manual dexterity will be assessed using the Nine Hole Peg Test (9HPT) [33], Purdue Pegboard Test [34] and the Coin Rotation Test (CRT) [35]. All these tests have previously been used and validated among MS patients [33,36,37]. The 9HPT requires the participant to place and then remove nine pegs, one at a time, into nine holes on a board as quickly as possible. The test is performed separately with each hand, and the time taken to complete the task is recorded. Shorter completion times indicate better manual dexterity. The Purdue Pegboard Test involves placing as many pins as possible into holes on a board. It includes subtests for the dominant and non-dominant hand, both hands simultaneously, and an assembly task. Higher scores reflect better dexterity. CRT assesses the coordination and speed of the fingers by rotating a coin clockwise with three fingers of the hand (thumb, index and middle finger) as fast as possible.

Satisfaction and adherence with the intervention will be recorded with the Sport Injury Rehabilitation Adherence Scale (SIRAS) [38]. This test consists of three clinician-rated items scored on a 5-point Likert scale (1–5): (1) the intensity of effort with which the patient completes the rehabilitation exercises (from minimum effort to maximum effort), (2) the extent to which the patient follows instructions and advice (from never to always), and (3) the patient’s receptivity to changes in the rehabilitation program (from very unreceptive to very receptive). In this context, a score of 1 reflects minimal engagement, whereas a score of 5 indicates optimal adherence. Although originally developed within a sports medicine context, the SIRAS evaluates three universal behavioral components of physical rehabilitation: the patient’s intensity of effort, adherence to clinician instructions, and receptivity to therapeutic changes. Because these observational metrics assess the active, behavioral aspects of patient engagement during supervised sessions—rather than being dependent on the physical etiology of the condition—the SIRAS provides a valid, reliable, and highly transferable measure of session adherence among MS patients.

#### 2.4.6. Sample Size Calculation

The sample size has been calculated using the software G*Power 3.1.9.7 (3.1.9.7v; Statistical Power Analyses for Windows, Universität Düsseldorf, Germany). The calculation was based on the COMP tool. According to a previous study [39], assuming an effect size of 0.7 for the COMP tool, an alpha value (α) of 0.05, a power (1 − β) of 0.80, and a 1:1 randomization ratio, a total of 52 patients will be needed. Assuming a 10% dropout rate, a total of 58 participants should be included in this study (29 participants in the experimental group and 29 participants in the control group).

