#### 2.4.7. Statistical Analysis

Data analysis will be performed using the Statistical Package for the Social Sciences version 24 (SPSS v24). A fully licensed version of SPSS is available through the university tp which the corresponding author of this manuscript belongs.

Descriptive statistics will be used to summarize the sample characteristics. Qualitative variables will be presented as percentages (%), while quantitative variables will be reported as mean ± standard deviation or as median and interquartile ranges (IQR).

The statistical distribution of the data will initially be assessed using the Shapiro–Wilk test. To ensure baseline balance, demographic characteristics and initial assessments will be compared between groups using independent samples *t*-tests for normally distributed data, the Mann–Whitney U test for non-normally distributed variables, and Chi-square tests for categorical data.

The primary analysis of the intervention’s effect will be conducted using a two-way mixed-design ANOVA, with ‘Group’ (Experimental vs. Control) as the between-subjects factor and ‘Time’ (Pre- vs. Post-intervention) as the within-subjects factor. The Group × Time interaction will be the primary effect of interest to determine efficacy. In the event of significant interactions, post hoc pairwise comparisons with Bonferroni correction will be performed.

Two-sided 95% confidence intervals will be calculated, and statistical significance will be set at *p* ≤ 0.05. No subgroup or exploratory analyses are planned for this study to maintain adequate statistical power.

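### The sample of 52 does not support the stated 80% power for the planned two-sided Group × Time test; the inputs give 52 for a two-group t-test only if it is one-sided

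*Protocol article*

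**What the plan says.** Section 2.4.6 (Sample Size Calculation) reports a G*Power calculation on the Canadian Occupational Performance Measure. The effect is introduced by "assuming an effect size of 0.7 for the COMP tool". Alpha is put at 0.05 and power at 80%, and the result reads "a 1:1 randomization ratio, a total of 52 patients will be needed". The target is then raised to allow for 10% of patients being lost, so that "a total of 58 participants should be included in this study", with equal groups of 29. The section does not say which G*Power test was used, whether it was one- or two-tailed, or which standard deviation scales the 0.7.

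Section 2.4.7 (Statistical Analysis) makes the Group × Time interaction of a mixed ANOVA (two groups, pre and post) the primary effect. It adds "Two-sided 95% confidence intervals will be calculated" and sets significance at p ≤ 0.05. No one-sided test and no correlation between repeated measures is stated anywhere in the article.

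**The concern.** A standardised difference of 0.7 at two-sided 5% and 80% power usually calls for somewhat more than 30 patients per arm, so 26 per arm looks low. With two groups and two time points, the interaction F-test is the same test as a two-sided t-test on change scores, so the planned analysis is two-sided whatever setting was used for the sample size.

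At stake is how a null result would be read. The protocol makes a formal power claim, says that the interaction is to determine efficacy, and gives the protection of power as its reason for planning no subgroup analyses. If the real power is lower, a negative finding would be presented as coming from an 80%-powered trial when it did not.

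**Working it through.** **Inputs from section 2.4.6:** d = 0.7, alpha = 0.05, power = 0.80, 1:1 allocation, 10% dropout. **From section 2.4.7:** non-directional interaction test, two-sided 95% intervals, p ≤ 0.05.

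**Formula.** For a two-sample t-test with n per arm, the noncentrality is δ = d·√(n/2) with 2n − 2 degrees of freedom. Power is the probability that a noncentral t exceeds the critical value, plus the negligible opposite tail when two-sided.

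**Step 1: reproduce the plan's figure (one-sided 5%).**
- n = 25: power 0.787.
- n = 26: δ = 0.7 × √13 = 2.524, critical t(50) = 1.676, power 0.801.
- The minimum is 26 per arm, a total of 52. Dropout: 52/0.9 = 57.8, so 58. Both published numbers are reproduced, and the dropout step is correct.

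**Step 2: same inputs, two-sided 5%.**
- n = 33: power 0.7997, just short.
- n = 34: power 0.812.
- The minimum is 34 per arm, a total of 68. Dropout: 68/0.9 = 75.6, so 76. The normal approximation gives 33 per arm (66), also far from 52.

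**Step 3: two-sided power at the planned size, with 0.7 as the standardised difference in change scores.**
- 26 per arm: δ = 2.524, critical t(50) = 2.009, power 0.697.
- 29 per arm: δ = 0.7 × √14.5 = 2.666, critical t(56) = 2.003, power 0.745.
- Effect detectable with 80% power: d = 0.79 with 52 evaluable, 0.75 with 58.

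**Step 4: 0.7 scaled by the raw-score SD instead.** With equal variances and pre-post correlation r, the SD of change is the raw SD × √(2(1 − r)). The effect on the change scale is therefore 0.7/√(2(1 − r)). The article gives no r, so the values below are assumptions:

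| r (assumed) | d on change scale | Two-sided power, 52 evaluable | N for 80% |
|---|---|---|---|
| 0.3 | 0.592 | 0.55 | 92 |
| 0.5 | 0.700 | 0.70 | 68 |
| 0.6 | 0.783 | 0.79 | 54 |
| 0.7 | 0.904 | 0.89 | 42 |

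**Step 5: other routes to 52.** Two non-directional calculations also give 52, each with an assumed r = 0.5.
- Repeated-measures ANOVA, between-factors (group main effect), f = 0.35: noncentrality f²·N·2/(1 + r). N = 50 gives 0.7996 and N = 52 gives 0.815.
- Baseline-adjusted comparison (ANCOVA): effective d = 0.7/√(1 − r²) = 0.7/√0.75 = 0.808. With 26 per arm, power is about 0.815, and 52 is the smallest total that reaches 80%.

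Neither is the interaction test. G*Power's interaction option with f = 0.35 and r = 0.5 gives N = 20, not 52.

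**The case against.** The strongest objection concerns cause. A reader might infer that the sponsor ran a one-sided calculation. The article does not say so. One-sided is the simplest setting that reproduces 52 from the listed inputs, but step 5 shows that a different G*Power module with an undeclared correlation could also have produced it. The fault might be the wrong module rather than the wrong tails. This stands, so the one-sided origin should be worded as an inference. It does not rescue the figure, because neither alternative is the planned interaction test and both need a correlation that the article does not declare.

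The second objection concerns size. A reader might infer that the true power is simply 70%. That holds only if 0.7 is a change-score effect, or a raw-score effect with r = 0.5. On the raw-score reading, power with 52 evaluable is close to 80% at r = 0.6 and above it at r = 0.7, but only about 55% at r = 0.3. This also stands: the shortfall has to be given as a range with its conditions. Because no correlation is stated, the article cannot claim 80% on that basis either.

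Third, the article calls the trial a pilot. That softens the consequence, but the article still makes a formal 80% power claim and aims to evaluate effectiveness. Nor is this a matter left to a fuller document, since the published sample size and the published test disagree with each other.

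**Conclusion.** The concern holds in conditional form. As a two-group comparison, the listed inputs lead to 52 only with one tail, whereas the planned test is two-sided and needs 68 evaluable (76 randomised). The stated 80% is therefore not supported for the planned analysis.

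Taking 0.7 as the standardised difference in change, the chance of missing that effect is about 30% with 52 evaluable (1 − 0.697), or about 25% if nobody drops out (1 − 0.745), against the 20% implied. Taking it as a raw-score effect, the shortfall could be larger or could vanish, depending on a correlation that the article does not give. The arithmetic is certain. What cannot be settled from the article is which G*Power setting was used and which SD scales the 0.7.

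**What to change.** Keep 58 randomised and rewrite the paragraph in section 2.4.6. State the G*Power test, the number of tails, the SD that standardises 0.7 and any assumed pre-post correlation. Then replace the 80% claim with the two-sided power of the planned test. If 0.7 is a change-score effect, suitable wording is: *52 evaluable participants give about 70% power at two-sided alpha 0.05 for a standardised difference in change of 0.7, or 80% power for 0.79.* If 0.7 is a raw-score effect, give the power at the assumed correlation and over a plausible range.

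If the primary analysis is changed to a baseline-adjusted one, state the power on that basis: about 81–82% with 52 evaluable at an assumed r = 0.5 and a raw-score effect of 0.7, and lower for smaller r (about 74% at r = 0.3). If 80% power for the interaction test at a change-score effect of 0.7 is to be kept, the alternative is 68 evaluable, or 76 randomised.

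The cost of the wording change is one paragraph and a less favourable stated power, with no extra patients. Recruitment is due to stay open until July 2026, so the paragraph should be corrected before any analysis.
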